### Analysis

Primary outcome analyses at 12 months will be by intention-to-treat. Descriptive statistics will be used to summarize the baseline and clinical characteristics of participants in each arm. To obtain correct inferences and improve power and efficiency, we will use a logistic regression model to estimate intervention effects, adjusting for sex and number of tests overdue at baseline (the stratification factors) as well as the following pre-specified prognostic factors: rurality, age at diagnosis, and attachment to primary care. The intervention effect will be expressed as an adjusted odds ratio together with a 95% confidence interval. Results will be converted to relative risks and risk differences which will be used to calculate the number needed to treat [33]. The number needed to treat is the inverse of the absolute risk difference.

The primary outcome analysis will be the completion of at least one test, but secondary analyses will explore whether results differ according to the type of test. We will conduct separate analyses for each test among eligible childhood cancer survivors. The secondary outcome of being fully up-to-date according to guidelines at the time of outcome assessment will be analyzed as described for the primary outcome. Health services utilization outcomes (e.g., number of outpatient visits over the prior 12 months or 24 months) will be analyzed using negative binomial regression, adjusting for the stratification factors.

Secondary analyses will consider the subgroup of participants in the intervention arm who are exposed to the full intervention (i.e., those who opt-in to receive their personalized information kit). Subgroup analyses in both the intention-to-treat and per-protocol populations will also be carried out to examine effect modification for the primary outcome by sex, number of tests required (1 vs 1 +), type of test required, rurality, neighborhood-level socioeconomic status, age at diagnosis, current age, and attachment to primary care. Ontario Health will transfer the deidentified study administrative dataset to the Ottawa Hospital Research Institute for analysis.

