### Population

As of February 28, 2021, there were just over 12,200 (18 +) childhood cancer survivors living in Ontario and 3284 of these survivors were at risk for one or more breast cancer, colorectal cancer, or cardiomyopathy based on their childhood cancer treatment. Our recent study found that many of these survivors were overdue for recommended surveillance: 92% of survivors at risk for breast cancer, 87% at risk for colorectal cancer, and 48% at risk for cardiomyopathy [unpublished data].

Eligible childhood cancer survivors will be recruited across Ontario. The ONLOOP Trial will be conducted in partnership with Ontario Health, the government agency responsible for health care planning and delivery across the province. Ontario Health holds multiple linked administrative datasets that allow it to measure health system performance. The research office at Ontario Health has established protocols to conduct studies involving patient contact. This study will leverage this infrastructure at Ontario Health to i) identify eligible survivors via analysis of linked administrative data and ii) invite these individuals to participate.

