### Allocation

After the study cohort has been created, Ontario Health will randomize eligible survivors into either the intervention or delayed intervention (control) arm using a 1:1 allocation ratio (Fig. 3). An independent statistician at Ontario Health will use a computer-generated random sequence to allocate survivors stratified by sex and whether the survivor is overdue for breast cancer, colon cancer, or cardiac surveillance. The study cohort will be allocated simultaneously, minimizing risks of bias due to lack of allocation concealment. There is a small risk of contamination if a survivor from the intervention group speaks with a survivor from the delayed intervention group, which may bias results towards the null.

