### Sample size

The sample size for this population-based study is fixed by the available number of eligible childhood cancer survivors. We previously identified 1724 childhood cancer survivors (53% of the POGONIS subset of 3268 childhood cancer survivors at risk for breast cancer, colorectal cancer, and/or cardiomyopathy) who were overdue for one or more of the recommended breast, colon, and/or cardiac tests as of 28 February 2021. Therefore, we anticipate allocating at least 862 individuals to each trial arm (intervention and control). Based on our prior analyses of administrative data [34], we estimate the uptake of recommended tests in a 12-month period will be 15% without any intervention (i.e., control arm proportion). Our anticipated sample size is sufficient to detect an absolute increase in the proportion of childhood cancer survivors with one or more tests completed as small as 6% (or a relative increase of 1.4) with 90% power in our intention-to-treat analyses. While a difference of 6% is considered relevant and important on a population level, it is expected that among those fully exposed to the intervention, the effect could be substantially higher. Loss-to-follow-up is anticipated to be minimal given the use of administrative data for outcomes.

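### The Allocation and Analysis sections name different stratification factors: which surveillance is overdue in one, how many tests are overdue in the other

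*Protocol article*

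**What the plan says.** Allocation section: eligible survivors are randomised all at once "using a 1:1 allocation ratio", and the random sequence is "stratified by sex and whether the survivor is overdue for breast cancer, colon cancer, or cardiac surveillance". The second factor is therefore defined by the kind of surveillance that is overdue. A count of tests is not mentioned.

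Analysis section: the primary outcome is analysed by logistic regression, "adjusting for sex and number of tests overdue at baseline (the stratification factors"). The remaining covariates are the "pre-specified prognostic factors: rurality, age at diagnosis, and attachment to primary care". Type of overdue test is not in the list.

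Two further analyses depend on the same definition. The outcome of being fully up to date is analysed as the primary outcome is. The health service utilisation counts "will be analyzed using negative binomial regression, adjusting for the stratification factors", and the factors are not listed again there.

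The subgroup list in the Analysis section includes "number of tests required (1 vs 1 +), type of test required", so the plan itself treats number and type as two variables.

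**The concern.** The parenthesis in the Analysis section asserts that the adjustment set is the set used to stratify the randomisation. Against the Allocation section that is not so. This is a conflict between two positive statements about the same item. It is not a detail left to the analysis plan, and an analysis plan written from this text would have two incompatible sources.

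Two things are at stake. First, the section gives correct inference and better power as its reasons for adjusting. If allocation was balanced on type and type is prognostic, a model without type has standard errors that are somewhat too large and gives up some precision. Second, the covariate set of the primary model should be settled before outcomes are seen. With two definitions in print, an analyst could later defend either of two models that give different odds ratios. The sample is fixed by the eligible population, so lost precision cannot be recovered by recruiting more.

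**Working it through.** **1. Can the two descriptions mean the same thing?**

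- *A single overdue yes/no.* The Sample size section describes the cohort as "overdue for one or more of the recommended breast, colon, and/or cardiac tests". A yes/no factor would be constant, so the Allocation factor must mean which surveillance is overdue.
- *Number as shorthand for type.* The subgroup list names both separately.
- *Number determining type.* Three overdue indicators (breast, colon, cardiac) give 2³ − 1 = 7 possible patterns in this cohort. Number has 3 levels: 1 covers three patterns, 2 covers three, and 3 covers one. Someone overdue only for echocardiography and someone overdue only for colonoscopy both score 1 but differ in type. The indicators fix the number; the number does not fix the indicators.
- *Type entering through another covariate.* Rurality, age at diagnosis and attachment to primary care do not carry it. Sex does so only in part, for breast surveillance.

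No reading removes the conflict.

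**2. The plan's own power figure**

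Inputs from the Sample size section: 862 per arm, 15% versus 21%, 90% power. Two-sided alpha of 0.05 is assumed, in line with the 95% confidence interval.

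Pooled proportion = (0.15 + 0.21)/2 = 0.18.

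z = [0.06 × √862 − 1.960 × √(2 × 0.18 × 0.82)] / √(0.15 × 0.85 + 0.21 × 0.79)
= (1.7616 − 1.0649) / 0.5417 = 1.286, so power = 90.1%.

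The requirement is 860 per arm without continuity correction. The stated 90% reproduces, and this point does not change it.

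**3. What adjusting for number instead of type would cost**

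The documents give no uptake by test type and no mix of overdue patterns, so this step rests on assumptions:

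- 1,724 survivors, 47% women.
- Pattern shares in women: breast only 12%, colon only 12%, cardiac only 46%, breast + colon 5%, breast + cardiac 12%, colon + cardiac 8%, all three 5%.
- Pattern shares in men: colon only 20%, cardiac only 65%, colon + cardiac 15%.
- Allocation 1:1 within each sex-by-pattern stratum.
- Odds ratio = (0.21/0.79)/(0.15/0.85) = 1.51, the value implied by the design.
- 2,000 simulated trials per setting. One model adjusts for sex and number, the other for sex and pattern.

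| Assumed 12-month control uptake (breast / colon / cardiac) | Power, number | Power, pattern |
|---|---|---|
| 10% / 8% / 14% | 88.4% | 88.6% |
| 4% / 4% / 18% | 88.8% | 89.5% |
| 2% / 2% / 20% | 89.5% | 90.6% |
| 2% / 30% / 5% | 77.3% | 80.7% |

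Overall control uptake was about 14% to 16%, near the planned 15%. The loss is about 0 to 1 point in the first three settings and 80.7 − 77.3 = 3.4 points in the last, which is deliberately extreme.

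Type I error was 4.3% to 5.2% with number and 4.7% to 5.6% with pattern. Its Monte Carlo error is √(0.05 × 0.95/2000), about 0.5 points, so neither model shows inflation.

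**The case against.** The strongest reply is that this is a wording slip of little consequence. Several parts of it stand.

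- *The documents do not settle which section is wrong.* A reader might infer that randomisation definitely used type and that number is not a randomisation factor. The Analysis section says outright that number is one, and the Allocation sentence could be loose shorthand. The trial schema in Fig. 3 was not available for this check. Only the conflict is established.
- *Type may not be strongly prognostic.* A reader might take the Population section's figures, "92% of survivors at risk for breast cancer, 87% at risk for colorectal cancer, and 48% at risk for cardiomyopathy", as proof that uptake differs by test. They are proportions overdue among all at-risk survivors. The trial enrols only survivors already overdue and measures completion over the next 12 months. For that, the Sample size section gives one pooled rate of 15%. The figures are no measure of uptake by type in this cohort and carry no weight here.
- *The inference is not invalid.* A reader might conclude that the stated aim of correct inference fails. The test keeps its size and is at most slightly conservative. Any change in the odds ratio reflects a different conditioning set, since odds ratios are non-collapsible, and results are also to be converted to relative risks and risk differences.
- *Type is partly covered.* Sex is in the model and the Background section describes breast surveillance in women. Separate analyses by test and a subgroup analysis by type are also planned.
- *The utilisation models are not a second error.* Their sentence is correct if read with the Allocation section, and ambiguous only because of the earlier parenthesis.

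What the reply does not remove is that the primary model is specified by reference to a design feature the document describes in two incompatible ways.

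**Conclusion.** The conflict is real and concerns the specification of the primary analysis. If the Allocation section is right, the primary and up-to-date models omit a randomisation factor, and the term used for the negative binomial models is unclear. If the Analysis section is right, the Allocation section misdescribes the randomisation and the models are sound.

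In the first case the expected cost is slightly conservative standard errors and a small loss of efficiency: about 0 to 1 point of power in ordinary settings, up to about 3 if uptake differs sharply by test. These sizes depend wholly on the assumed test mix and uptake. Type I error is not inflated, the comparison is not tilted toward the intervention, and the sample size and stated 90% power are unaffected. Severity is minor to moderate. The case for acting is that the covariate set should be unambiguous before outcomes are seen.

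**What to change.** Check the allocation program to establish which factors were used. Then reconcile the two sections before any outcome data are seen, and name the factors explicitly for the primary, up-to-date and negative binomial models.

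- *If type was used:* adjust for sex plus three indicators (overdue for cardiac, for breast, for colon), or for the sex-by-pattern stratum. Number may stay as an extra covariate or a subgroup variable, but should not be called a stratification factor.
- *If number was used:* correct the Allocation section and leave the models as they are.

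The cost is one check of the allocation program and a sentence or two of text. No new data collection is needed, because overdue status by test is established when the cohort is created. The sample size does not change.

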#### Secondary outcomes

(1) Completion of each type of surveillance test (among those eligible for the test); (2) being fully up-to-date with their surveillance tests; (3) number of outpatient visits to primary care professionals and cancer specialists; (4) number of emergency department visits and hospitalizations to understand the impact on health system resources.

Study outcomes in both study arms will be analyzed at 12 months and 24 months after study cohort randomization.

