### Data collection

This is a registry-based trial [26] with data collection from existing administrative databases held at Ontario Health. We will primarily rely on Ontario Health Insurance Program billing data to assess whether and when each childhood cancer survivor completed their mammogram/breast MRI, colonoscopy, and/or echocardiography. If applicable, the Ontario Breast Screening Program and Gastrointestinal Endoscopy datasets will also be used to assess the completion of these tests. See Table 2 for data sources for primary and secondary outcomes.

**Table 2 Tab2:** Primary and secondary outcomes and data sources

Outcomes	Definition	Data source
Primary outcome		
Any Test Completion	- Completion of any of the recommended surveillance tests (binary)	Ontario Health Insurance Program, Ontario Breast Screening Program, Gastrointestinal Endoscopy
Secondary outcomes		
Echocardiography	- Completion of echocardiography (binary)	Ontario Health Insurance Program
Colorectal cancer screening	- Completion of colorectal cancer screening (binary)	Ontario Health Insurance Program, Gastrointestinal Endoscopy
Breast cancer screening	- Completion of breast cancer screening (binary)	Ontario Health Insurance Program, Ontario Breast Screening Program
Up-to-date surveillance	- Completion of all the recommended surveillance tests (binary)	Ontario Health Insurance Program, Ontario Breast Screening Program, Gastrointestinal Endoscopy
Primary care visits	- Number of outpatient visits to primary care provider (count)	Ontario Health Insurance Program
Oncologist/aftercare visits	- Number of outpatient visits to oncologists and/or AfterCare Clinics (count)	Ontario Health Insurance Program [27, 28], Pediatric Oncology Group of Ontario Networked Information System, Corporate Provider Database, Client Agency Program Enrolment, Virtual rostering (using existing Ontario Health algorithms)
Hospitalizations	- Number of hospitalizations among survivors of childhood cancer (count) - Cause of hospitalization	Discharge Abstract Database
Emergency department visits	- Number of emergency department visits among survivors of childhood cancer (count) - Cause of emergency department visit	National Ambulatory Care Reporting System
Population characteristics	- Demographics, socioeconomic and ethno-racial status, rurality	Postal Code Conversion File, Ontario Marginalization Index, Registered Persons Database

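### The negative binomial models for the secondary utilization counts omit each survivor's own pre-randomization count, which gives away precision, mainly for frequent outpatient visits

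*Protocol article*

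**What the plan says.** The Analysis section gives one rule for all utilization outcomes: they "will be analyzed using negative binomial regression, adjusting for the stratification factors". Earlier in the section the factors are identified in the primary model, described as "adjusting for sex and number of tests overdue at baseline (the stratification factors"). The Allocation section words the second factor differently, by which kind of surveillance is overdue. On either wording, neither factor measures how much care a person uses.

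The primary logistic model is given a wider set. It adds "pre-specified prognostic factors: rurality, age at diagnosis, and attachment to primary care", and the stated reason for the approach is efficiency: "To obtain correct inferences and improve power and efficiency, we will use a logistic regression model". These extra covariates are not carried over to the count models.

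The example outcome in the utilization sentence, "number of outpatient visits over the prior 12 months or 24 months", might be mistaken for a baseline measure. It is the outcome window, because the Secondary outcomes section states: "Study outcomes in both study arms will be analyzed at 12 months and 24 months after study cohort randomization".

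On sources, the Data collection section describes "data collection from existing administrative databases held at Ontario Health". Table 2 assigns primary care visits to the billing data, hospitalizations to the discharge database and emergency visits to the ambulatory care database. The section on study cohort and participants has Ontario Health link the cohort to administrative datasets and determine overdue status before allocation.

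**The concern.** A person's earlier use of a service is usually informative about later use of the same service. In a randomized comparison of skewed, over-dispersed counts, adjusting for it removes between-person variation that would otherwise sit in the standard error of the rate ratio. The protocol accepts this reasoning for its primary model but fixes a narrower covariate set for the counts and gives no reason.

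What is at stake is the width of the intervals on the utilization outcomes. The Secondary outcomes section includes emergency and hospital counts to learn about the effect on health system resources. A wide interval leaves added burden neither shown nor excluded. The Sample size section says the number of survivors is fixed by how many are eligible, so precision cannot be bought by enrolling more people. Covariate adjustment is one of the few means left.

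**Working it through.** **1. The plan's own figure.** The only stated power concerns the primary outcome: 862 per arm, 15% against 21%, 90%. Two-sided alpha of 0.05 is assumed, as none is stated. With pooled proportion 0.18:

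z = (0.06 × √862 − 1.96 × √(2 × 0.18 × 0.82)) / √(0.15 × 0.85 + 0.21 × 0.79) = (1.7616 − 1.0649) / 0.5417 = 1.286, which gives power of 90.1%.

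The matching sample size is 860 per arm. The figure reproduces, and this point does not touch it. No power or precision is stated for the counts.

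**2. Inputs for the counts.** From the protocol: 1724 survivors, 1:1 allocation, negative binomial regression. Assumed, because the documents give nothing: mean counts per year, person-level frailty variance, and the correlation between the counts before and after randomization.

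**3. Method.** Counts for the two periods were simulated as Poisson with correlated lognormal person-level frailties (log-frailty correlation 0.4, 0.7 and 0.9), no treatment effect, 100 replicates per setting. A negative binomial model with arm alone (SE₀) was compared with arm plus log(1 + prior count) (SE₁), using mean model standard errors of the log rate ratio.

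- Variance reduction = 1 − (SE₁/SE₀)²
- Equivalent sample size = 1724 × (SE₀/SE₁)²
- Narrowing of the interval on the log scale = 1 − SE₁/SE₀

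**4. Results.** Variance reduction and equivalent sample size come from unrounded standard errors.

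| Mean per year (frailty variance) | Count correlation | SE₀ | SE₁ | Variance reduction | Interval narrower by | Equivalent N |
|---|---|---|---|---|---|---|
| 4 (1.0) | 0.26 | 0.0476 | 0.0460 | 7% | 3% | 1845 |
| 4 (1.0) | 0.50 | 0.0476 | 0.0421 | 22% | 12% | 2206 |
| 4 (1.0) | 0.69 | 0.0476 | 0.0372 | 39% | 22% | 2825 |
| 1 (2.0) | 0.18 | 0.0742 | 0.0730 | 3% | 2% | 1782 |
| 1 (2.0) | 0.39 | 0.0746 | 0.0698 | 13% | 6% | 1971 |
| 1 (2.0) | 0.55 | 0.0743 | 0.0654 | 23% | 12% | 2229 |
| 0.5 (2.0) | 0.14 | 0.0906 | 0.0897 | 2% | 1% | 1756 |
| 0.5 (2.0) | 0.29 | 0.0907 | 0.0875 | 7% | 4% | 1850 |
| 0.5 (2.0) | 0.42 | 0.0903 | 0.0842 | 13% | 7% | 1984 |
| 0.1 (4.0) | 0.06 | 0.1740 | 0.1737 | 0.4% | 0.2% | 1730 |
| 0.1 (4.0) | 0.14 | 0.1755 | 0.1739 | 2% | 1% | 1756 |
| 0.1 (4.0) | 0.24 | 0.1745 | 0.1707 | 4% | 2% | 1801 |

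Example, second row: 1 − (0.0421/0.0476)² = 0.22, and 1724 / (1 − 0.2186) = 2206.

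**5. Limits of the check.** The comparison model held arm alone, without sex or overdue tests. If those factors already carry some of the information in the prior count, the gain over the planned model is smaller. The mean model standard error fell in every setting. Empirical standard errors from 100 replicates are noisy: in the last row the adjusted one was slightly larger (0.1712 against 0.1655), while in the second row the empirical variance reduction was 42%.

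**The case against.** The best defence is that nothing here is an error. Negative binomial regression adjusted for the stratification factors is a sound analysis of over-dispersed counts in a randomized trial. The outcomes are secondary, with no stated power, margin or decision rule. The article condenses a fuller plan, and extra covariates for secondary models are often left to that plan. The benefit also depends on correlations that no document reports, and a variance reduction overstates what a reader of the interval would see: 22% less variance is a 12% narrower interval.

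Most of this stands as a limit on size and importance. It does not remove the point. The article does not leave the covariates open. It names them, and names fewer than for the primary model, whose approach it justifies by efficiency.

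A reader might infer more than the documents support:

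- **That the cost results suffer.** The Economic evaluation section derives costs from cost macros and estimates incremental cost with generalized estimating equations and bootstrapping. The negative binomial models are not described as an input, and no covariates are fixed for the cost regression, so there is no stated choice to correct.
- **That the primary logistic model needs prior testing history.** That is a different model, and no gain has been quantified.
- **That the gain is similar for visits, emergency attendances and hospitalizations.** It shrinks towards nothing as events become rare.
- **That the change has no drawback.** Extraction of earlier utilization counts is never expressly listed. Availability is a strong inference from the linkage and look-back already planned, and survivors without full coverage in the earlier year would have incomplete counts.

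**Conclusion.** The point holds as a low-cost gain in precision on a stated modelling choice. The planned count models are valid, no figure in the protocol becomes wrong, and the primary analysis is unaffected.

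The gain could be material for frequent outpatient visits if use is stable from year to year, modest at around one event or fewer per year, and close to nil for rare events. Which of these applies to primary care, specialist, emergency and hospital counts cannot be settled from the documents, because they give no event rates. The direction is well supported. The size is not, because it depends on assumed means, dispersion and correlations and on a comparison without the stratification factors.

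**What to change.** State, before outcome data are seen, that each negative binomial model adjusts for the stratification factors and also for log(1 + the survivor's count of the same outcome in the 12 months before randomization). Use the same baseline window for the 12-month and 24-month analyses. Add a simple rule for survivors whose records do not cover the full look-back year, for example a missing-look-back indicator, so that nobody is dropped.

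The cost is one more extracted variable per outcome, the look-back rule and a sentence of text. No contact with survivors is needed. The effect is still reported as a rate ratio. Fixing the covariate in advance matters because adding it after results are known would look selective. The cost regression and the primary logistic model need no change on this account.

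### The opt-in and per-protocol analyses rest on a post-randomisation choice that controls cannot make within 12 months, so an effect read from them mixes the programme's effect with willingness to engage

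*Protocol article*

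**What the plan says.** The primary analysis is by intention-to-treat. The Analysis section then adds two things. First, "Secondary analyses will consider the subgroup of participants in the intervention arm who are exposed to the full intervention", which it explains as those who opt in to receive the personalised kit. Second, "Subgroup analyses in both the intention-to-treat and per-protocol populations will also be carried out to examine effect modification" for the primary outcome, over eight factors: sex, number of tests required, type of test, rurality, neighbourhood socioeconomic status, age at diagnosis, current age and attachment to primary care.

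The Recruitment section says that the toolkit and the 6-month reminder go only to survivors who actively opt in. The Delayed intervention (control) arm section gives controls no contact for 12 months (13 months in Blinding and in Step 1). The Sample size section adds that "it is expected that among those fully exposed to the intervention, the effect could be substantially higher".

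The article names no comparator, estimand or method of handling selection for the opt-in or per-protocol analyses.

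**The concern.** Membership of the fully exposed group is decided after randomisation, by the survivor, and in one arm only. Would-be enrollees certainly exist in the control arm, but they cannot be identified over the 12-month window. A per-protocol analysis of effect modification needs a control group. The evident candidate is the whole uninvited control arm, which mixes people who would and would not have signed up. Comparing it with enrollees alone gives up the protection of randomisation.

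Survivors who return a consent form may well be more inclined to be tested anyway, and the process evaluation itself plans to look for factors that explain engagement. The covariates listed for the primary model (sex, number of tests overdue, rurality, age at diagnosis, primary care attachment) do not measure motivation, and the article does not say whether they apply to these analyses.

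The trial is meant to inform whether ONLOOP becomes a permanent programme. A favourable figure for enrollees could be over-read, above all if the intention-to-treat result were null.

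**Working it through.** **1. The plan's own figure.** Inputs from Sample size and Allocation: "we anticipate allocating at least 862 individuals to each trial arm", "using a 1:1 allocation ratio", "we estimate the uptake of recommended tests in a 12-month period will be 15% without any intervention", and a detectable increase "as small as 6% (or a relative increase of 1.4) with 90% power in our intention-to-treat analyses". Two-sided alpha of 0.05 is assumed, in line with "The intervention effect will be expressed as an adjusted odds ratio together with a 95% confidence interval".

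- Pooled rate: (0.15 + 0.21)/2 = 0.18.
- Null SE: √(2 × 0.18 × 0.82/862) = 0.01851.
- Alternative SE: √((0.15 × 0.85 + 0.21 × 0.79)/862) = 0.01845.
- Power: Φ((0.06 − 1.96 × 0.01851)/0.01845) = Φ(1.29) = 0.90.

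The stated 90% reproduces (860 per arm needed, 862 planned).

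**2. Enrollees against all controls when nothing works.** Two inputs are not in the documents and are assumed: the opt-in share q (10% to 50%) and the ratio R of background completion in would-be enrollees to that in the rest (1 to 2). Letter and toolkit have no effect, and overall completion stays at 15%:

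- q·p_opt + (1 − q)·p_non = 0.15, with p_opt = R·p_non.
- Spurious difference: p_opt − 0.15 = 0.15 (R − 1)(1 − q)/(1 + q(R − 1)).

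Example, q = 0.30 and R = 2:

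- p_non = 0.15/1.3 = 11.5% and p_opt = 23.1%, so the difference is +8.1 points.
- With 259 enrollees and 862 controls, the pooled rate is 0.1687, the null SE 0.0265 and the alternative SE 0.0289.
- Rejection probability: Φ((0.0808 − 1.96 × 0.0265)/0.0289) = 84%.
- A simulation of 4,000 trials gave +8.1 points and 85% rejection for this contrast, against 4.7% for intention-to-treat.

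| Opt-in share | Enrollees | R = 1 | R = 1.5 | R = 2 |
|---|---|---|---|---|
| 10% | 86 | 0; 5% | +6.4; 36% | +12.3; 80% |
| 20% | 172 | 0; 5% | +5.5; 44% | +10.0; 87% |
| 30% | 259 | 0; 5% | +4.6; 42% | +8.1; 84% |
| 40% | 345 | 0; 5% | +3.8; 37% | +6.4; 76% |
| 50% | 431 | 0; 5% | +3.0; 29% | +5.0; 62% |

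Each cell gives the spurious difference in percentage points and the share of trials with p < 0.05, unadjusted for covariates.

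**3. A randomisation-based alternative.** The complier-average effect is the intention-to-treat risk difference divided by q. It is zero when the intention-to-treat effect is zero. If a 6-point effect acts only through enrollees, it is 6/0.3 = 20 points at q = 30%. The direct contrast with R = 2 would give 20 + 8.1 = 28 points.

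**4. Sensitivity to the letters.** If the invitation and reminders change completion by λ among non-enrollees, the effect in enrollees is (ITT − (1 − q)λ)/q. With ITT = 6 points and q = 30%:

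- λ = +2 points: (6 − 1.4)/0.3 = 15.3 points.
- λ = −1 point: (6 + 0.7)/0.3 = 22.3 points.

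**The case against.** The strongest reply is that the article never says enrollees will be compared with all controls, and that a full protocol or analysis plan may name a sound estimator. This stands in part: the comparator is inferred, and a missing estimator alone would be no finding. But the article does more than omit detail. It commits to an exposed subgroup defined in one arm by a post-randomisation choice, and to effect-modification analyses in a per-protocol population, which need a comparator that cannot be matched on opt-in at 12 months.

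Several stronger readings are tempting and are not supported:

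- **That a large spurious benefit is to be expected.** Its size depends on q and R, which the documents do not give. With no selection it is zero, and at R = 1.5 with half opting in it is 3 points. Everyone in the cohort is already overdue, and most survivors are described as unaware of their surveillance needs, which may limit selection.
- **That the Sample size remark shows selection being taken as confirmation.** A larger effect among the exposed is also what simple dilution of an intention-to-treat effect implies, as the 6 and 20 points above show.
- **That the trial's main conclusion is at risk.** The primary analysis and its power are by intention-to-treat, and the economic evaluation uses the primary outcome.
- **That controls can never opt in.** This holds for the 12-month window. They are invited afterwards, so it does not carry over unchanged to the 24-month outcomes.

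It is also fair to object that the complier-average effect has a weak point here. It requires that the letters do nothing to those who do not sign up. The Recruitment section makes the invitation part of the intervention, and Step 1 has it carry information on late effects and the importance of surveillance. That objection stands, so the assumption must be stated and varied.

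**Conclusion.** The concern holds for the secondary analyses at 12 months. An effect estimate for enrollees, or effect modification in a per-protocol population, is open to selection bias that the listed covariates do not measure. Under the assumed range (R from 1.5 to 2, opt-in from 10% to 50%, no true effect, 15% overall completion, unadjusted contrast with all controls), the bias is about +3 to +12 points, with nominal significance in about 29% to 87% of trials. For scale, the trial is powered for 6 points. These figures show what could happen; they do not predict what will. The primary intention-to-treat analysis and its 90% power stand.

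**What to change.** 1. Run the effect-modification analyses in the intention-to-treat population only.
2. Replace the per-protocol effect estimate at 12 months with a complier-average causal effect: the intention-to-treat risk difference divided by the intervention-arm opt-in proportion, with a bootstrap confidence interval, labelled exploratory.
3. State that it assumes the invitation and reminder letters have no effect on those who do not sign up, and that this is doubtful here. Show the estimate over a range of non-zero letter effects, as in step 4 of the working. Call it an upper bound only if the letters can be taken not to deter testing.
4. Label any direct description of enrollees as non-causal.
5. Do not use control-arm survivors who sign up after the delayed invitation as a matched comparator for months 0 to 12. Their opt-in follows that outcome and may depend on it. With 23.1% background completion among would-be enrollees, and completers half as likely to sign up later, control opt-ins would show 0.1154/(0.1154 + 0.7692) = 13.0%. A programme with no effect would then appear to add 10 points.

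The cost is wording and a short calculation from intervention-arm opt-in, which the process evaluation already tracks. The price is an assumption that must be stated and a wider interval. With no effect, q = 30% and R = 2, the intention-to-treat half-width is 1.96 × √(2 × 0.1275/862) = 3.4 points. Divided by 0.3 (q treated as fixed) it becomes about 11.2 points, against 1.96 × 0.0289 = 5.7 points for the direct contrast.
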